## Outcomes

3

### Primary outcome

3.1

The primary outcome measure is the number of intrusive memories of traumatic event(s) reported in the diary daily during Week 5 (i.e., for 7 days, from Day 29–35 post-intervention). Participants will receive four links per day (via SMS and email) to record their number of intrusions for morning, afternoon, evening and night respectively, via the electronic platform SMART-TRIAL, starting four weeks after the intervention (i.e., Day 29 post-intervention). Participants will be asked *‘How many intrusive memories did you have during the morning/afternoon/evening/night’* and will be presented with a drop-down menu of 9 possible responses (i.e., ‘0’, ‘1’, ‘2’, ‘3’, ‘4’, ‘5’, ‘6’, ‘7’, ‘more than 7*’).* If a participant selects ‘more than 7’, they can manually enter any number higher than 7.

The link will include a brief description of what intrusive memories are, and the following instructions about how to monitor their occurrence in the diary:*‘Intrusive memories are IMAGES from a traumatic event that pop suddenly into your mind, when you DO NOT WANT them to. (They are NOT the same as deliberately choosing to think about the event or thinking about it in words.) Please record EVERY intrusive memory you have had - even if it is the same one popping up several times. If you did not have any, please CHOOSE 0.’*

In addition to this brief description, participants will receive more detailed instructions prior to commencing the diary (e.g., in an animated information video about the symptom ‘intrusive memories’, 1:50 min, and via guided researcher support, see also 2.6.1). The diary has been employed in feasibility and pilot work for the current trial in electronic form (i.e., in the SMART-TRIAL platform) [15], as well as in previous work conducted by the group in pen-and-paper form [20]. We note that analysis of the primary outcome will seek to take into account baseline scores, which may be highly variable across participants.

### Secondary outcomes

3.2

#### Number of intrusive memories of traumatic event(s) (during Week 0 and Week 1)

3.2.1

Number of intrusive memories of traumatic event(s) reported in a diary daily during Week 0 and Week 1 (as per the primary outcome).

#### Impact of Event Scale - revised (IES-R), intrusion subscale [32]

3.2.2

Self-report measure that assesses subjective distress after a traumatic event (with reference to study event[s]) in the last week. We will administer the intrusion subscale (8-items). Items are rated on a 5-point scale from 0 (“not at all”) to 4 (“extremely”) and summed; a higher score indicates worse outcome. The IES-R possesses high internal consistency (α = 0.96) as well as high agreement with other measures of posttraumatic stress symptomatology e.g., the PTSD Checklist (r = 0.84) [33]. The IES-R intrusion subscale has been a focus of our previous work [20,25].

#### Impact of Event Scale - Revised (IES-R), avoidance subscale [32]

3.2.3

Self-report measure that assesses subjective distress after a traumatic event (with reference to study event[s]) in the last week. We will include the avoidance subscale (8-items). Items are rated on a 5-point scale from 0 (“not at all”) to 4 (“extremely”) and summed; a higher score indicates worse outcome.)

#### Posttraumatic Stress Disorder Checklist 5 (PCL-5), short version [36]

3.2.4

The PCL-5 short version includes 8 items assessing PTSD symptoms in the last month (or in the last week-at 1-week follow-up) [36]. Items are rated on a 5-point scale from 0 (“not at all”) to 4 (“extremely”). Total scores range from 0 to 32; higher scores indicate greater severity. The PCL-5 short version has an extremely high correlation with the original, accounting for 94.1% (r = 0.97) of the variance in the original 20-item validated PCL-5 version [36]. It has been specifically recommended for remote digital assessment after trauma [37].

#### Self-estimated intrusion frequency to explore convergence with diary measure

3.2.5

##### Intrusion Questionnaire (IQ) - frequency item [47]

3.2.5.1

A single item measuring the frequency of intrusive/unwanted memories of the traumatic event(s) in the previous week, on a 7-point scale ranging from “never” to “many times a day”. When applicable, participants are asked a follow-up question to specify the exact number of intrusions they have experienced per day.

#### Characteristics of intrusive memories

3.2.6

##### Intrusion questionnaire (IQ) - characteristics [47]

3.2.6.1

Five self-rated items measuring characteristics of intrusive/unwanted memories in the previous week; specifically: level of intrusion-related distress, nowness, reliving, disconnectedness and whether different triggers are associated with the intrusive/unwanted memories of the traumatic event(s). Items are rated from 0 to 100; higher scores indicate more distress, nowness, sense of reliving, feelings of disconnection, and more triggers associated with the intrusive/unwanted memories. Previous studies that have used the intrusion questionnaire have included four rating scales: frequency, distress, vividness, nowness. Retest-reliability for these four scales has ranged between r = 0.61 and r = 0.72 [48]. Each item is analysed separately, see Table 1.

##### Distress and vividness of intrusive trauma memories during diary weeks

3.2.6.2

Two self-rated items assessing the level of distress and vividness associated with intrusions (11-point scales, ranging from 0 to 10) rated within the diary at baseline (Week 0), Week 1 and Week 5; higher scores indicate higher levels of distress and vividness. Each item is analysed separately, see Table 1. This measure is referred to as “Characteristics of intrusive trauma memories” in the Clinical Trials registration.

### Other outcomes and assessments

3.3

Other outcomes will include general and occupational functioning, as well as the perceived impact of intrusive memories on functioning, items assessing intervention/control task procedures (e.g., to assess adherence to protocol) and feedback items to assess acceptability of the intervention. See Table 1 for an overview of when each measure will be administered.

**Table 1 tbl1:** Schedule of assessments.

Assessments	Week 0 D-7 to −1	Baseline D1	Task D1	Week 1 D1 to 7	1-week D8	1-month D29	Week 5 D29 to 35	5-weeks D35	3-months D85	6-months D169
***Demographics and participant information***										
Informed consent	X									
Inclusion/exclusion criteria	X									
Randomisation			X							
Demographics		X								
Type and number of traumatic event(s) during the COVID-19 pandemic leading to IMs		X			X	X			X	X
Time the traumatic event(s) leading to IMs occurred		X								
Clinical Background		X								
LEC-5 (prior trauma)		X								
***Primary outcome***										
Number of intrusive memories of traumatic event(s) in diary							X			
***Secondary outcomes***										
Number of intrusive memories of traumatic event(s) in diary	X			X						
IES-R intrusion subscale		X			X	X			X	X
IES-R avoidance subscale		X			X	X			X	X
PCL-5 shortened version		X			X	X			X	X
*Self-estimated intrusion frequency to explore convergence with diary measure*										
IQ-frequency		X			X	X		X	X	X
*Characteristics of intrusive memories*										
IQ characteristics - distress		X			X	X			X	X
IQ characteristics - nowness		X			X	X			X	X
IQ characteristics - reliving		X			X	X			X	X
IQ characteristics - disconnectedness		X			X	X			X	X
IQ characteristics - triggers		X			X	X			X	X
Distress of IMs during diary week		X			X			X		
Vividness of IMs during diary week		X			X			X		
***Other outcomes and assessments***										
*Perceived impact of intrusive memories on functioning*										
Concentration disruption from IMs - level		X			X	X		X	X	X
Concentration disruption from IMs - duration		X			X			X		
Concentration and memory difficulties										X
Impact of IMs on occupational functioning		X			X	X			X	X
Impact of IMS on functioning in other areas		X			X	X			X	X
SCI-02		X			X	X			X	X
Examples of IM impact (open-ended)*								X		
*Perceived functioning and social support*										
Social support after traumatic event		X			X	X			X	X
Self-rated health		X			X	X			X	X
Questions related to work situation		X			X	X			X	X
Sick leave		X			X	X			X	X
SEQ - stress subscale		X			X	X			X	X
Letting go of work-related thoughts		X			X	X			X	X
Moral stress at work		X			X	X			X	X
SWEBO – burnout subscale		X								X
Coping (open-ended)		X								
WHODAS 2.0										X
*Other cognitive assessments*										
Appraisals of IMs – psychological problems		X			X	X			X	X
Appraisals of IMs – negative self-evaluations		X			X	X			X	X
TPQ – past		X			X	X			X	X
TPQ – present		X			X	X			X	X
TPQ - future		X			X	X			X	X
FSQ – vividness									X	
FSQ – positivity									X	
FSQ – perspective									X	
*Assessments related to procedures*										
Adverse Events					X	X			X	X
Credibility/Expectancy questionnaire			X							
Subjective Units of Distress (SUDS)			X							
List of intrusive memories (only intervention arm)*			X							
Adherence to intervention/control task instructions*			X							
Number of booster sessions delivered by researcher*							X			
Number of days/nights at work during intrusion diary weeks*		X			X			X		
*Feedback to assess acceptability and improve materials and procedures for implementation*										
Feedback questionnaire						X				
Open-ended feedback questions*			X		X	X		X	X	X

*Note.* *assessments not listed in CTR as they are assessments related to procedures rather than outcome measures or have open ended responses. Abbreviations: IMs = intrusive memories; LEC-5 = Life Events Checklist for DSM-5, IES-R = Impact of Event Scale – Revised, SCI-02 = Sleep Condition Indicator two-item version, PCL-5 = Posttraumatic Stress Disorder Checklist for DSM-5, SEQ=Stress Energy Questionnaire, SWEBO=Scale of Work Engagement and Burnout, WHODAS 2.0 = World Health Organization Disability Assessment Schedule 2.0, IQ=Intrusion questionnaire, TPQ = Time Perspective Questionnaire, FSQ=Future Self Questionnaire.

#### Perceived impact of intrusive memories on functioning

3.3.1

##### Self-rated concentration disruption associated with intrusive memories – level and duration

3.3.1.1

Rating scale derived from Holmes et al. (2017) [3]**.** One item measures the level of concentration disruption associated with the intrusions (‘How much did your intrusive memories disrupt your concentration during the previous week?‘) on an 11-point scale (from 0 to 10); a higher score indicates greater disruption. Another item measures the estimate Self-estimated intrusion frequency to explore convergence with diary measured duration of concentration disruption of each intrusion (‘When you have an intrusive memory, for how long does it disrupt your concentration [in minutes]?‘; <1 min, 1–5 min, 5–10 min, 10–30 min, 30–60 min, > 60 min).

##### Concentration and memory difficulties [38,39]

3.3.1.2

Eleven items assess the extent of concentration and memory difficulties during the previous four weeks, using a 5-point scale (1 “Virtually every day” to 5 “Never”). Total scores range from 11 to 55; higher scores indicate less concentration and memory difficulties.

##### Self-rated impact of intrusive memories on functioning

3.3.1.3

Rating scale derived from Iyadurai et al. (2019) [2]***.*** Two items assess the extent to which intrusive memories have an impact on occupational functioning or daily functioning in other areas of life (e.g., social, housework, parenting, etc), using an 11-point scale (0 “no impact” to 10 “extreme impact”) and a free text response field to provide details. Each item is analysed separately, see Table 1. This measure is referred to as “Self-rated functioning” in the Clinical Trials registration.

##### Sleep Condition Indicator (SCI-02) [34]

3.3.1.4

Two items assess sleep – i.e., participants (i) rate the extent to which they experienced poor sleep (with reference to the study event(s)) on a 5-point scale (from “not at all” to “very much”), and (ii) indicate how many nights they experienced sleep problems per week on a 5-point scale (from 0 to 1 nights to 5–7 nights) as used in our earlier work [35]. Each scale is reverse scored and summed, with a higher total score indicative of better sleep. The test–retest reliability and intraclass correlation coefficient (ICC) have been reported as r = 0.68 and ICC = 0.68 respectively [34]. The SCI-02 is highly correlated with the full eight-item version of the SCI (r = 0.80) [34]. This measure is referred to as “Self-rated sleep ratings” in the Clinical Trials registration.

##### Examples of impact of intrusive memories on functioning

3.3.1.5

Two bespoke free text response fields which ask participants to provide an example of how a specific intrusive memory has had a negative impact on functioning, and if a specific intrusive memory has reduced, how this has had a positive impact on functioning.

#### Perceived functioning and social support

3.3.2

##### Social support after traumatic event

3.3.2.1

One item measuring perceived social support, asking participants to indicate how much social support they received after the traumatic event(s), rated on an 11-point scale (0 “no support” to 10 “a lot of support”).

##### Self-rated health (SRH)

3.3.2.2

One item assessing perceived health on a 7-point scale (from “very good” to “very bad”) [40]. The scale is reverse scored, high scores indicate good outcomes.

##### Questions related to work situation [41]

3.3.2.3

Three free response questions (e.g., which type of health care do you work with right now? (only administered at Day 1) and two free response questions on whether the work situation changed and if yes, how.

##### Sick leave [41]

3.3.2.4

Two bespoke items measuring the total number and the number of full work days on sick leave because of reason for seeking health care. Higher numbers indicate more sick leave. Each item is analysed separately, see Table 1.

##### Stress Energy Questionnaire (SEQ), stress subscale [42]

3.3.2.5

Three items measuring the number of times participants have felt stressed, pressured, or tense at work during the previous week on a 5-point scale (from “never” to “several times per day”). The three items are summed; higher sum scores indicate higher levels of stress. In a recent study with nurses, the internal consistency reliability was α = 0.96 [43]. Additionally, one item measures difficulties in letting go of work-related thoughts during leisure time (from “very rarely or never” to “very often or always”) [44], and another question asks whether the abovementioned difficulties are due to participants’ intrusive memories (yes/no response).

##### Moral stress at work [41]

3.3.2.6

Five items assess how much moral stress one feels at work, using a 4-point scale ranging from 1 (“strongly agree”) to 4 (“strongly disagree). All items are summed, with higher scores indicative of lower levels of moral stress.

##### Scale of Work Engagement and Burnout (SWEBO), burnout subscale [45]

3.3.2.7

Nine items measuring symptoms of burnout on three subscales: exhaustion, disengagement, and inattentiveness. Items are rated on a 4-point scale, from 1 (“not at all”) to 4 (“all the time”) and summed; a higher sum score indicates a higher level of overall burnout. Reliability scores for the burnout dimension range from r = 0.77 to 0.88 [45].

##### Coping

3.3.2.8

Two bespoke free response questions assessing participants’ perceived coping during the COVID-19 pandemic (i.e., “Based on your experiences and from your perspective, are there any specific situations or factors during the COVID-19 pandemic, that you think made it particularly difficult for you to cope?” and “Based on your experiences and from your perspective, are there any specific factors which you think have made it easier for you to, cope with the COVID-19 pandemic and its consequences?”).

##### WHODAS 2.0

3.3.2.9

12 self-rated items assessing functioning in six life domains: 1) cognition, 2) mobility, 3) personal care 4) relations, 5) daily activities and 6) participation in society. Each item is rated on a 5-point scale, from 1 (“none”) to 5 (“extreme or cannot do”) and summed; a higher sum score indicates worse functioning. An additional three questions are asked at the end regarding the frequency and impact of these items. WHODAS 2.0 has shown high internal consistency (α = 0.83 to 0.92) and adequate construct validity [46].

#### Other cognitive assessments

3.3.3

##### Appraisals of intrusive memories [49]

3.3.3.1

Six self-report items (11-point scale from 0 to 100) measuring appraisals of having intrusions on two subscales: psychological problems (α = 0.94) and negative self-evaluations (α = 0.81) [50]. Items for each subscale are summed, with higher values indicative of worse appraisals [50].

##### Time Perspective Questionnaire (TPQ) [51]

3.3.3.2

Eight self-report items measuring participants’ time perspective on three subscales: past perspective (α = 0.85 to 0.87), present perspective (α = 0.78 to 0.83), and future perspective (α = 0.71 to 0.75) [51]. All items are rated on a 5-point scale, from 1 to 5, and summed per subscale; higher values indicate a greater sense of past/present/future time perspective.

##### Future Self Questionnaire (FSQ), shortened version, based on [52]

3.3.3.3

A free response question asking participants to imagine their future self-identity (e.g., ‘I will be a mother”). Participants will also be asked to describe a mental image of this identity, and rate the vividness (from 1 “not vivid at all” to 10 “very vivid”) and positivity (from 1 “very negative” to 10 “very positive”) of the image. Participants will also rate the perspective from which they view the mental image (“through own eyes” or “as if seeing oneself”). Participants will make each of these ratings twice, to indicate their responses both before and after the traumatic event(s). Each item is analysed separately, see Table 1.

#### Assessments related to procedures

3.3.4

##### Adverse events

3.3.4.1

A free response question in which participants indicate whether they have experienced any health issues since their last contact with the study team.

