#### Booster procedures

2.5.5

Participants in both conditions will be informed that they can contact the research team at any time during the study; thus, will have the option to e.g., ask the research team for researcher-guidance, including advice about the repeated use of the task procedure, or to ask any other questions they may have about the study procedures. In the first researcher-guided session, participants in both conditions will be informed that they can repeat the task procedure on their own (i.e., option for self-administered booster doses).

Participants in both conditions will be asked to monitor the number of intrusions they experience in the week following the first session (i.e., Week 1 diary) and can receive reminders from the research team if they stop filling in the diary (see 2.6.6).

As described above (see 2.6.3), participants in the intervention condition will be encouraged to repeat the intervention if they experience persistent intrusive memories. They could do this in two ways – either (a) use the gameplay task procedure directly after experiencing an intrusion, or (b) as the former is not always practical in daily life, they could set aside a time to do the intervention by deliberately recalling the specific memory that is persistent (i.e., gently bring to mind the image that had intruded) and then complete the gameplay task procedure. Monitoring of intrusive memories in the diary is a means by which the participant can notice whether a booster session may be useful.

Participants in the control condition will not be given instructions to repeat the task if they experience an intrusive memory. On balance, we did not consider it justified at this stage in the research to (after a first session) ask healthcare staff during the pandemic to engage in a task hypothesized to be non-active but potentially time consuming.

For participants in the intervention group only, ‘boosters’ (self-administered or researcher-guided) can be initiated by the research team. Researchers will monitor incoming diary data in the intervention condition during Week 1. In the event that a participant continues to report persistent intrusive memories after the initial intervention session, the researcher will contact the participant to:1)ask them if the intrusion/s was/were from the most recently targeted image (i.e., the image selected in the first guided sessions with the researcher or in a self-administered booster); or a non-targeted image.

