#### Both conditions: completion of daily diary (Week 1 and 5) and follow-ups

2.5.6

Participants in both conditions will be asked to complete an intrusive memory diary and monitor the occurrence of any intrusive memories each day during Week 1 (secondary outcome) and Week 5 post-intervention (primary outcome). Participants will be asked to record the number of intrusive memories they experience each day during the week and to record zero if they did not experience any intrusions. The diary in the electronic platform is accessed via a link received by SMS or email (see 3.1).

Once they have completed the diary for each monitoring period (i.e., on the 7th day of each diary week), participants will be asked to provide overall ratings of intrusion vividness, intrusion-related distress and the extent to which intrusive memories affected their concentration during the past week. They will also be asked how many days, as well as nightshifts, they have worked during the previous week. Additionally, at the end of the Week 5 diary, participants will be asked if they can give an example of (a) how a specific intrusive memory has had a negative impact on their functioning, and (b) if a specific intrusive memory has reduced in number, how this has had a positive impact on their functioning.

Incoming diary data will be monitored by a researcher approximately once a day. Participants in both conditions will be contacted as necessary (e.g., if they cease to complete the digital diary to provide support regarding how to use it).

Participants in both conditions will complete secondary and other outcome measures and note the occurrence of any adverse events on day 7 (1-week). Follow-up measures will also be administered at 1-month, 3-months, and 6-months post-intervention. Data will be collected remotely/digitally (e.g., computer or smartphone) via a secure platform (i.e., SMART-TRIAL [28]). To promote participant retention and data collection, we will be flexible regarding the mode of collection of outcome measures (i.e., we include the option to collect them via telephone, SMS, or on paper if necessary), guided by participant preference.

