### Adverse events

3.4

We will screen for adverse events (at 1-week, 1-month, 3-month, and 6-month follow-ups) using a brief self-report form (‘Have you had any health problems since the last contact’ [yes/no], if yes is answered: ‘Briefly describe which:‘) used by our local clinical trials unit (KTA).

Any adverse events reported (whether spontaneously reported by the participant to study personnel or during follow-ups in the electronic platform SMART-TRIAL) will be registered in an adverse event log. Adverse events will be classified as serious or not. Adverse events will be assessed for severity (mild, moderate or severe) and relationship to intervention (not related, unlikely, possible, probable, definite) by the Principal Investigator. Any actions taken will be logged.

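### Adverse events are asked about since the last team contact, but only the intervention arm has team-initiated booster contacts, so ascertainment may differ by arm

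*Protocol article*

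**What the plan says.** Two places in the protocol article describe the adverse-event item. Section 3.3.4.1 states that "participants indicate whether they have experienced any health issues since their last contact with the study team". Section 3.4 gives the wording put to participants, "Have you had any health problems since the last contact", and schedules it "at 1-week, 1-month, 3-month, and 6-month follow-ups". Table 1 places these at Days 8, 29, 85 and 169, identically for both arms. Neither section ties the look-back period to a date, to the Day 1 session or to the previous form.

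Section 3.4 also enters every reported event in a log, "whether spontaneously reported by the participant to study personnel or during follow-ups in the electronic platform SMART-TRIAL".

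Section 2.5.5 reserves team-initiated boosters for the intervention group: "Researchers will monitor incoming diary data in the intervention condition during Week 1". If a participant "continues to report persistent intrusive memories after the initial intervention session, the researcher will contact the participant to" establish which image is intruding, a full guided booster, a phone call or an SMS may follow. The protocol describes all three as contact with the researcher.

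Other contacts are open to both arms. Section 2.5.6 says that "Participants in both conditions will be contacted as necessary", for example when diary entries stop. Section 2.5.5 allows any participant to approach the team at any time.

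**The concern.** A safety comparison between arms needs the same question over the same period. Here the start of the period depends on when the team last spoke or wrote to the participant, and one arm has an additional, protocol-defined source of such contacts. That source depends on allocation and on symptoms reported after randomisation.

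On the literal wording, an event between the Day 1 session and a Day 4 booster call is never asked about, because no adverse-event question is scheduled at the call and the Day 8 form looks back only to Day 4. It enters the log only if the participant volunteers it. The booster call is also an extra occasion for volunteering, which works the other way.

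What is at stake is the comparability of the adverse-event data, above all in the week closest to the task. The primary outcome and the sample size are not involved.

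**Working it through.** The article states no adverse-event rate, booster frequency or booster timing, so there is no figure of its own to reproduce. The check uses the days in Table 1: session on Day 1, adverse-event forms on Days 8, 29, 85 and 169. (Section 2.5.6 puts the 1-week measures on day 7; Table 1 is used here.)

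**Step 1. Windows with no interim contact.** 8 − 1 = 7, 29 − 8 = 21, 85 − 29 = 56 and 169 − 85 = 84 days; in total 7 + 21 + 56 + 84 = 168 days.

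**Step 2. Literal reading with a last contact on Day k of Week 1.** The window at the Day 8 form is 8 − k days. The loss is (k − 1)/7 of that window and (k − 1)/168 of all follow-up.

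| Contact day k | Days left in window | Loss of the 7 days | Loss of the 168 days |
|---|---|---|---|
| 2 | 6 | 1/7 = 14% | 1/168 = 0.6% |
| 4 | 4 | 3/7 = 43% | 3/168 = 1.8% |
| 7 | 1 | 6/7 = 86% | 6/168 = 3.6% |

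These are losses for one contacted participant, not for the arm.

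**Step 3. Arm level, illustration only.** Assume that events are spread evenly over time, that a share f of the intervention arm is last contacted on Day k, and that a pre-contact event is volunteered with probability s. Let r be the probability that an event is captured when there is no interim contact. First-week capture in the intervention arm, relative to an arm without interim contacts, is

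1 − f × (k − 1)/7 × (1 − s/r).

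None of f, k, s and r is in the article. With f = 0.5, k = 4 and r = 1:

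- s = 0: 1 − 0.5 × 3/7 = 79%
- s = 0.5: 1 − 0.5 × 3/7 × 0.5 = 89%
- s = 1: 100%

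Replacing 7 by 168 gives the whole of follow-up: 99.1%, 99.6% and 100%.

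**Step 4. Direction.** The expression falls below 1 when s < r and rises above 1 when s > r. If participants mention health problems on a call more readily than they enter them on a form, the intervention arm is over-counted relative to control; if less readily, it is under-counted. The article settles neither.

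**Step 5. Alternative reading.** If the last contact means the previous scheduled assessment, the windows are 7, 21, 56 and 84 days in both arms and the loss is zero.

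**The case against.** The strongest reply is that, in a form repeated at fixed follow-ups, the last contact can naturally mean the last assessment, and then nothing is lost. If every study message counted instead, the four diary links per day in diary weeks (section 3.1) would shrink the window in both arms and largely remove the difference. This stands as far as it shows that the term is undefined. It does not dispose of the point: section 3.3.4.1 speaks of contact with the study team, which fits a researcher's call or SMS better than an automated link, and nothing in the article equates it with the previous form.

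Other parts of the reply stand:

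- A reader might infer that events in the intervention arm are under-counted. The article does not support that, because events volunteered during booster contacts are logged (Step 4).
- A reader might picture a full window in every control participant. Diary support and participant-initiated contacts can shorten it there as well. The booster contacts come on top of these, in one arm.
- A reader might extend the effect to the 1-, 3- and 6-month forms. The monitoring that triggers team contact is specified for Week 1. Later boosters are possible, but no arm-specific scheme after Day 8 is described.
- A reader might take the contacted participants to be those doing worst. Contact also follows intrusions of images not yet targeted, which section 2.5.3 expects to need their own session. That does not mark deterioration.

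How events are tabulated by arm is ordinarily left to the statistical analysis plan, and its absence here is no fault.

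**Conclusion.** The point holds in limited form. The only solicited adverse-event item has an undefined anchor, and one class of contact that could move that anchor occurs by design in one arm only. Adverse-event ascertainment may therefore differ between arms, mainly at the 1-week form.

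For a contacted participant, the solicited window at that form is 14% to 86% shorter, or 0.6% to 3.6% of total follow-up. This assumes the literal reading and a last contact between Day 2 and Day 7. A larger claim, such as a halving of first-week events in the arm, would need a booster timing and frequency that the article does not give, and would need spontaneous reports to add nothing. The net difference could go either way and could be nil.

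**What to change.** Reword the item to a fixed anchor: since the Day 1 session at 1 week, and since the previous scheduled adverse-event form at 1, 3 and 6 months. Windows are then 7, 21, 56 and 84 days in both arms, however many booster contacts take place. Record in the log whether each event was solicited on a form or reported spontaneously, so that the two can be separated when arms are compared.

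The cost is modest but not nil. Recruitment began on September 30, 2020, the form is one used by the local clinical trials unit, and earlier protocol changes went through ethics amendments. A change now means a minor amendment and two versions of the item, so the version used should be recorded with each form. For forms already collected, section 3.3.4.6 records the date of each researcher-delivered booster session, so forms that follow such a session can be identified. This is only partial, because SMS contacts may not be recorded as sessions.
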